# **Data Linkage**

Many of the study participants in Stage 1 are expected to have already participated in a previous research study with our team (UQ DRC). In these instances, where participants have agreed, we plan to use data and samples collected from the previous research study, in the current study. This may include; questionnaire data and genetic sequencing results. Specifically, questionnaire data relating to health behaviour and sun protection will be used to produce longitudinal data when combined with the current study. The previous studies that participants may have been involved in with UQ-DRC are under Metro South HREC references; HREC/09/QPAH/162, HREC/16/QPAH/37, HREC/16/QPAH/125, and HREC/17/QPAH/816.

A separate consent page on the PICF explains the data linkage explicitly, and requires participants to separately consent to this aspect of the study.

# **Genetic Sequencing**

Saliva samples will be collected using an Oragene DNA self-collection kit (DNA Genotec), or similar. The sample will be sent to an NATA accredited genetic testing laboratory in the USA for panel testing of known genes associated with melanoma risk (Invitae Melanoma Panel). This process only involves looking at specific genes, and does not involve searching for novel genetic changes or markers in techniques such as Whole Exome Sequencing. Therefore, it is not possible to have any *incidental findings*, in which a gene mutation associated with an unrelated condition is found. As we are using a panel test that will cover multiple melanoma risk genes, it is therefore possible that a participant may be found to hold a second mutation that was not previously found in their family, and this may come as a surprise. This possibility is covered during the pre-testing genetic counselling and education. In the event that this occurs, appropriate genetic and/or psychological counselling will be provided (See Ethical Considerations section).

# **Data Analysis**

*7.1 Stage 1: Pre and post genetic counselling questionnaires*

All questionnaires used in Stage 1, are previously validated, with recommended protocols for quantitative analysis. In some cases, questionnaire responses will be pooled within previously defined groups (i.e. *CDKN2A* positive, other germline mutation positive, or no mutation found), and compared for significant statistical differences using paired t-tests or chi-square analysis. Differences between dermatologist and genetic counsellor reported results will also be analysed.

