In Australia, the majority of genetic testing for familial melanoma has been conducted in a research setting. Presently, in most cases the inclusion of genetic testing does not impact clinical management, as someone with extensive personal history would be managed as ‘high risk’ regardless of identified germline mutation. Therefore, the clinical utility of genetic testing for familial melanoma has been questioned^9^. Others have highlighted the benefit of genetic testing for ensuring appropriate surveillance in as yet, unaffected family members^10^. Clinical research studies, however, have continued to show positive outcomes for predictive testing in familial melanoma. Clinical trials have reported that any negative psychological impact of genetic testing is short term^10^, and learning of a genetic susceptibility has provided motivation for greater sun protective behaviour and screening^11^. Furthermore, reporting of negative *CDKN2A* mutation status provides relief for members of *CDKN2A* families, and assists them in re-adjusting to appropriate prevention strategies if previously overly cautious^12^. Importantly, there has been no evidence to suggest that a negative result has instilled a false sense of security, with several studies showing sun protective behaviour and skin examinations did not decrease^10, 13^, and in some studies, actually increased after disclosure of negative mutation status^14, 15^.

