# **2.2 Recruitment**

*2.2.1: Stage 1: Genetic counselling and education, questionnaires and phone interview*

Eligibility Criteria: Individuals who are identified as having a strong personal and/or family history of melanoma indicative of inherited risk, will be invited to join the study. The eligibility criteria is based on a recent publication by Taylor *et al* (2019), which describes a tool GenoMELPREDICT that can be used to predict *CDKN2A* mutational status in people from melanoma-prone families^20^. The criteria for a populations with moderate-to-high incidence of melanoma is 3 primary melanomas in an individual and/or families with ≥1 invasive melanoma and ≥2 other invasive melanoma and/or pancreatic cancer among first-degree or second-degree relatives on the same side of the family.

Individuals will be recruited from four sources;

1. A registry of previous participants kept by University of Queensland’s Dermatology Research Centre (UQ-DRC)
2. Selected QIMR Berghofer Medical Research Institute (QIMR Berghofer)’s  *Pathways from Genotype and Environment to MELANOMA*  study (ERM Project ID 25706 HREC/14/QPAH/495)
3. Family members of enrolled participants (with participants’ prior approval)
4. Referrals from local dermatologists or healthcare providers

Previous study participants of the UQ-DRC who are eligible for the study, will be contacted by phone and given a description of the current study to gauge interest in participation. A participant information and consent form (PICF) will be emailed out if there is interest in participating. Individuals will be encouraged to read through the document and discuss with family members and/or healthcare providers. Individuals will be recontacted 1-2 weeks after PICF has been sent out to discuss participation in the study, and to answer any questions individuals have. A time and date will be made for an appointment at the Clinical Research Facility at PA Hospital, at the participant’s convenience.

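### Stage 1 compares questionnaire outcomes by mutation result with unadjusted tests, leaving personal melanoma history as an unhandled potential confounder and effect modifier

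*Protocol*

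**What the plan says.** **Who enters.** Section 2.2.1 invites people with a "strong personal and/or family history of melanoma indicative of inherited risk". The rule is "3 primary melanomas in an individual and/or families with ≥1 invasive melanoma and ≥2 other invasive melanoma and/or pancreatic cancer" among near relatives on one side of the family. One listed recruitment source is "Family members of enrolled participants", provided they meet the testing criteria. Nothing in 2.2.1 requires the enrolled person to have had melanoma.

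**How the two kinds differ.** The Introduction says that "someone with extensive personal history would be managed as ‘high risk’ regardless of identified germline mutation". It then reports that others have pointed to "the benefit of genetic testing for ensuring appropriate surveillance in as yet, unaffected family members".

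**How outcomes are compared.** Section 2.1 fixes three analysis groups by mutation result. Subsection 7.1 says that, in some cases, "questionnaire responses will be pooled within previously defined groups" and compared by paired t-tests or chi-square. It also plans a comparison of dermatologist with genetic counsellor. Randomisation is stratified by family mutation status. No section splits, stratifies or adjusts by personal melanoma, although section 2.3.1 collects personal medical history at the first counselling session.

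**Which outcomes.** Table 1 measures sun exposure, skin surveillance and Cancer Worry at baseline, 3 months and 12 months, and risk perception at every time point.

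**The concern.** The Introduction sets out to explore whether psychological and behavioural outcomes depend on finding a familial mutation. Mutation result is not assigned at random. Someone with three primary melanomas may enter with no family history, whereas a relative enters through a pedigree. Entry route is therefore tied to personal melanoma and plausibly to mutation status as well.

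If people with and without melanoma change by different amounts, two problems follow. A difference between mutation groups may partly reflect disease history rather than the genetic result. And an average over a mixed group describes neither kind of participant well. What is at stake is the reading of an exploratory secondary comparison, and whatever it contributes to the Stage 2 questionnaire.

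**Working it through.** There is no plan figure to reproduce. Stage 1 size rests on data saturation, and no effect size, SD, alpha or power is stated. The calculations below show how the problem scales; they do not estimate it.

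**Inputs from the protocol.** About 50 participants (section 2.1). CDKN2A accounts for 20 to 40% of familial cases (Introduction). Applied to this sample, that gives 0.20 × 50 = 10 to 0.40 × 50 = 20 carriers.

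**Assumed inputs.** Change scores with SD 1; mean change 0.8 SD in unaffected and 0 in affected people; two-sided alpha 0.05; affected shares as listed.

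**1. Confounding.** With no mutation effect, the expected spurious difference (CDKN2A-positive minus the rest) is 0.8 × (share affected in the rest − share affected in carriers). Type I error comes from 10,000 simulated trials per scenario with 10, 15 or 20 carriers out of 50. The unadjusted analysis is a two-sample t-test on change. The adjusted analysis is a linear model with affected status added.

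| Affected: carriers vs rest | Spurious difference | Type I error, unadjusted | Type I error, adjusted |
|---|---|---|---|
| 50% vs 50% | 0.8 × 0 = 0 | 5.0–5.6% | 4.9–5.3% |
| 40% vs 60% | 0.8 × 0.20 = 0.16 SD | 7–8% | 4.6–5.2% |
| 30% vs 80% | 0.8 × 0.50 = 0.40 SD | 19–25% | 4.7–5.1% |
| 20% vs 90% | 0.8 × 0.70 = 0.56 SD | 33–45% | 4.7–5.2% |

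Bias after adjustment lay within ±0.01 SD. The simulated data follow the adjusted model, so this shows what the covariate can do when that model is right. Reversing the shares reverses the sign.

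**2. Effect modification.** Suppose instead that the affected share a is equal in both groups and that a mutation effect of 0.8 SD exists only in unaffected people. The pooled effect is (1 − a) × 0.8: 0.60, 0.40 and 0.20 SD at a = 25%, 50% and 75%. Power (normal approximation, 10 to 20 carriers) falls from 62–79% with nobody affected to 40–55%, 20–28% and 8–10%. The same multiplication applies to average pre/post change.

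**3. Precision cost of the covariate.** Take 15 carriers and 35 others.
- At 30% vs 80% affected, the overall share is (4.5 + 28)/50 = 0.65 and its variance 0.65 × 0.35 = 0.2275. The between-group part is 0.3 × 0.7 × 0.5² = 0.0525, so R² = 0.23. The standard error grows by √(1/(1 − 0.23)) = 1.14.
- At 40% vs 60%, R² = 0.0084/0.2484 = 0.034 and the factor is 1.02.

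Both factors are before any gain from lower residual variance.

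**The case against.** **This belongs in the SAP.** Only the protocol is at hand, covariates are often left to the SAP, and 7.1 does not forbid adjustment. That has weight. But sections 2.1 and 7.1 do fix the grouping and name the tests. Section 8.2 defers detail for Stage 2, and 7.1 has no such sentence for Stage 1. A better method than the one stated is available from data already collected.

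**A ceiling in affected people.** A reader might infer that affected participants are already under surveillance and cannot improve. The Introduction speaks of clinical management in people with extensive personal history, not of questionnaire scores or of every affected person. It also reports greater sun protection and screening after testing without limiting this to unaffected people. No ceiling is documented, least of all for worry.

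**Cancer Worry as fear of recurrence.** A reader might infer this from the title of the cited reference. The protocol plans no such interpretation, so there is nothing to correct.

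**The mix is unknown.** This stands. The Introduction at one point calls personal and family history together a prerequisite for testing, which suggests few unaffected people, though 2.2.1 admits either. Affected shares by mutation group are not given. Carriers could be affected more often than others, or less often if many are unaffected relatives from CDKN2A families.

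**Not every comparison is exposed.** Also correct. Subsection 7.1 pools only in some cases. The dermatologist comparison is randomised, so imbalance there is due to chance. A status fixed at baseline cannot confound within-person change; it can only modify it.

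**Small and exploratory.** The primary aim is qualitative, and Stage 2 (about 200 people) is meant to give the fuller dataset. This limits the priority, not the reasoning.

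**Conclusion.** The point holds in a limited form. Entry can be mixed, the Introduction itself separates people with extensive personal history from unaffected relatives, and the stated comparison of mutation groups is neither randomised nor adjusted for that distinction. Personal melanoma history is therefore a potential confounder of the mutation-group comparison and a potential modifier of pre/post behavioural change.

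The documents do not support saying that a bias exists, or in which direction. The confounding vanishes if affected shares are equal or if both kinds of participant change alike. It is modest at a 20-point gap in shares and serious only at gaps of 50 points or more, all under an assumed contrast of 0.8 SD versus none. Given exploratory secondary aims, the change is worth making but is not critical to the study.

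**What to change.** Amend Data Analysis, subsection 7.1, for skin surveillance, sun exposure, Cancer Worry and risk perception:

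1. Compare mutation groups with a regression model of the follow-up score (with baseline included) or of the change score, in a form suited to the outcome's scale. Include personal melanoma history (yes/no, from the first-session medical history) as a covariate. It is recorded before results are given, so it is a valid baseline variable.
2. Describe overall pre/post change separately for participants with and without personal melanoma, with confidence intervals and labelled exploratory.
3. Tabulate personal melanoma history by mutation group, so that readers can see whether the shares differ.

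Do not cross-split by the three mutation groups. That makes six cells from about 50 people. The Introduction puts each of eight further genes below 1% of familial cases; if enrolment mirrored this, the other-mutation group would hold fewer than 8 × 1% × 50 = 4 people.

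The cost is a change of wording with no new data. The adjusted estimate loses some precision: little if affected shares are similar, more if they differ widely. The two descriptive subsets will have wide intervals.

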# **Study Design**

# **2.1 Methods**

This study will be completed in two stages with two separate cohorts.

Stage 1: Genetic testing and counselling, semi-structured interview, and questionnaires at multiple time points. (n=50)

Stage 2: A one-off questionnaire designed after analysis from stage 1. (n=200)

The cohort for stage 1 of the study will be made up of approximately 50 participants (depending on when data saturation is reached in qualitative analysis of interviews). These participants will all have a suspected inherited risk of melanoma, and will be further stratified into 3 groups for data analysis, including a) those with a positive CDKN2A mutation, b) those positive for a different mutation for melanoma risk, and c) those where no mutation is found. All groups will receive pre and post genetic education and counselling, questionnaires at multiple time points (see table 2), and will participate in a semi-structured phone interview to discuss their experience with genetic testing and counselling one month after receiving test results.

Interview data will be transcribed and evaluated qualitatively using thematic analysis. Questionnaires will compose of validated instruments (see table 1), and will be analysed as per each scale’s manual and standard procedures. Findings produced by questionnaire and interview analysis will then be used to design a novel questionnaire instrument for capturing psychosocial and behavioural impact of genetic testing has for familial melanoma.

Stage 2 of the study will validate the novel questionnaire instrument in a cross-sectional study, enrolling a second cohort of approximately 200 participants with suspected familial melanoma. This second stage of the study will provide a more complete dataset from which hypotheses and conclusions about the psychosocial and behavioural impact genetic testing has for familial melanoma. This information will be a valuable addition to the current literature and inform genetic testing practices in the future.

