In most cases the second counselling session for test reporting will occur approximately. 2-3 months after their first visit. This visit will either take place at the CRF- PAH or over online video conference call using Zoom, and will take approx. 1 to 1.5 hours. The session will begin by asking the participant to complete a questionnaire with selected validated instruments (see table 1). The purpose of these questionnaires is to measure any impact from the first genetic education and counselling appointment. Once questionnaires are complete, a genetic counsellor (or trained dermatologist) from the research team will conduct the post testing genetic counselling and reporting of genetic testing results. This process includes: test results, significance for personal risk, significance for family risk, recommended preventative health behaviour and screening. The genetic counsellor or dermatologist will offer to send a report of the genetic findings to the participant’s nominated healthcare provider. At the end of the counselling session, the participant will be asked if they consent to being contacted for a phone interview at a later date.

Post genetic testing, education and counselling questionnaires will be conducted at 2 weeks, 3 months and 12 months following reporting of test results. These questionnaires will be sent using the REDCap System, which facilitates an email containing a web-link to be sent for the participant to complete the questionnaire online, at their convenience. Two reminder emails to complete questionnaires will be sent out if not completed.

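### Section 7.1 names only paired t-tests or chi-square for the Stage 1 questionnaires and does not separate within-person change from between-group comparison; chi-square on before/after answers would ignore the pairing and can miss change.

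*Protocol*

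**What the plan says.** Section 7.1 of the protocol, under Data Analysis, is headed "Stage 1: Pre and post genetic counselling questionnaires". It says that the instruments "are previously validated, with recommended protocols for quantitative analysis". In some cases "questionnaire responses will be pooled within previously defined groups", meaning CDKN2A positive, other mutation positive and no mutation found, and the responses are then "compared for significant statistical differences using paired t-tests or chi-square analysis". On the randomised comparison of providers it adds only this: "Differences between dermatologist and genetic counsellor reported results will also be analysed".

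The data are repeated measures. Under 2.3 Study Visits, participants complete questionnaires at baseline and at the second visit, and after that "questionnaires will be conducted at 2 weeks, 3 months and 12 months following reporting of test results". Table 1 lists sun exposure and skin surveillance at baseline, 3 months and 12 months. It gives no response format for them and, unlike for the scales, no reference. Section 2.1 adds that questionnaires follow each scale's manual and standard procedures, and that the Stage 1 cohort is "made up of approximately 50 participants (depending on when data saturation is reached in qualitative analysis of interviews". Yes/no and Likert answers are described only in 8.2, for the one-off Stage 2 questionnaire.

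**The concern.** One sentence covers two kinds of comparison and offers two tests without matching them. For change over time within a mutation group, the paired t-test fits and an ordinary chi-square does not. For a comparison between mutation groups or between providers, chi-square fits and a paired t-test cannot be done, because the people differ. On either reading, one of the two named tests does not suit the comparison. If both comparisons are meant, the analyst has to guess which test goes with which.

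The first reading raises the practical problem. A Pearson chi-square of wave by answer counts each participant twice, as if the two answers came from two people. A person's answers about a habit are usually positively correlated, and the test then uses too large a variance. Its false-positive rate falls below the nominal level and it loses power. Secondary aim 1 concerns the psychosocial and behavioural impact of education, counselling and testing. With about 50 participants, a real shift in a yes/no behaviour could be reported as no impact.

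**Working it through.** **The plan's own figures.** There are none to reproduce. The protocol gives no alpha, power, effect size or correlation for the questionnaires, and the cohort size rests on interview saturation.

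**Inputs.** From the protocol: about 50 Stage 1 participants, the same people at each wave. Assumed: all 50 answer both waves, two-sided alpha 0.05, a binary behaviour with proportion p1 before and p2 after, and within-person correlation (phi) from 0 to 0.7.

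**Formulas.**
- Covariance of the two answers: c = phi × √[p1(1−p1)p2(1−p2)].
- Discordant probabilities: yes-to-no b = p1(1−p2) − c; no-to-yes d = p2(1−p1) − c.
- True variance of the change in proportions: [(b+d) − (d−b)²]/n.
- Variance used by Pearson: 2p̄(1−p̄)/n, with p̄ = (p1+p2)/2.
- Null variance used by McNemar: (b+d)/n.
- Approximate power: Φ[(|p2−p1| − 1.96 × null SE)/true SE].

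**No true change (p1 = p2 = 0.5).** The true variance is (1−phi) times the one Pearson uses, so the actual error rate is about 2[1 − Φ(1.96/√(1−phi))].

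| phi | 1.96/√(1−phi) | Approximate size | Simulated size, n=50 |
|---|---|---|---|
| 0 | 1.96 | 5.0% | 5.7% |
| 0.3 | 2.34 | 1.9% | 2.3% |
| 0.5 | 2.77 | 0.6% | 0.7% |
| 0.7 | 3.58 | 0.03% | 0.1% |

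Asymptotic McNemar stays between 4.4% and 5.5% in the same simulated cases.

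**Change from 50% to 70%, n=50, phi = 0.5.**
- c = 0.5 × √(0.25 × 0.21) = 0.1146.
- b = 0.15 − 0.1146 = 0.0354; d = 0.35 − 0.1146 = 0.2354; b+d = 0.2709 (unrounded sum).
- True SE = √[(0.2709 − 0.04)/50] = 0.0680.
- Pearson SE = √(2 × 0.6 × 0.4/50) = 0.0980; power ≈ Φ[(0.2 − 0.1920)/0.0680] = Φ(0.117) ≈ 55%.
- McNemar SE = √(0.2709/50) = 0.0736; power ≈ Φ[(0.2 − 0.1443)/0.0680] = Φ(0.82) ≈ 79%.

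The normal approximation is rough at this size. Simulation of the paired 2×2 table (200,000 replicates per case) gives the figures to use:

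| n | Change | phi | Pearson | McNemar, asymptotic | McNemar, exact |
|---|---|---|---|---|---|
| 50 | 50% to 70% | 0 | 55% | 54% | 44% |
| 50 | 50% to 70% | 0.3 | 55% | 69% | 60% |
| 50 | 50% to 70% | 0.5 | 56% | 83% | 76% |
| 50 | 50% to 70% | 0.6 | 56% | 93% | 88% |
| 50 | 50% to 65% | 0.5 | 28% | 55% | 46% |
| 50 | 50% to 75% | 0.5 | 82% | 97% | 95% |
| 50 | 60% to 80% | 0.5 | 63% | 89% | 82% |
| 20 | 50% to 70% | 0.5 | 17% | 43% | 20% |

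A separate run of 20,000 replicates gives mid-p McNemar at n=50, 50% to 70%: 67% at phi 0.3 and 83% at phi 0.5. For a subgroup of 25 at phi 0.5 it gives Pearson 27%, exact 33%, mid-p 46% and asymptotic 51%.

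**Reading the tables.** For 50% to 70% at n=50, the loss against asymptotic McNemar is nil at phi 0, about 13 points at 0.3, 27 at 0.5 and 37 at 0.6. A change to 75% would usually be found even with the unpaired test.

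**The case against.** The strongest reply is that section 7.1 never assigns chi-square to before/after change. It maps no test to a data type, and comparing the three mutation groups with each other is a possible reading, for which chi-square is appropriate. Chi-square analysis is also a loose term: asymptotic McNemar is itself a chi-square statistic. The protocol points to each scale's own procedures, so the sentence is not an exhaustive list. Most repeated instruments are scored scales, and no response format is given for the behaviour items. A statistical analysis plan that is not shown may settle all of this. The misuse would also be conservative, in a secondary aim of a study whose primary aim is qualitative.

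Much of this stands. A reader might infer that the protocol prescribes an unpaired test for paired data, or that real changes are likely to be missed. The documents do not support either. The first is one reading of an ambiguous sentence. The second depends on a correlation and an effect that the protocol does not give.

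What does not stand is that the sentence is adequate. The between-group reading rescues chi-square only by making the paired t-test unusable. The pointer to scale procedures is weak for sun exposure and skin surveillance, for which Table 1 cites no source. Section 7.1 also differs from 8.2: it names tests, and it does not defer its methods to later development.

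**Conclusion.** The point holds as a matter of clarification with a conditional consequence. Section 7.1 should separate within-person change from comparisons between different people, and it names no paired method for categorical answers. If chi-square is used on before/after answers, the result is conservative and can miss real change.

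The size is conditional. It rests on 50 complete pairs, two-sided 5%, a binary item and positive within-person correlation, of which only the approximate cohort size comes from the protocol. For a 20-point rise from 50%, the cost runs from nothing at correlation 0 to about 27 points of power at 0.5, and more at higher correlation. If the behaviour items are analysed as scores, this loss does not arise. In mutation subgroups of about 20 the number of people is the main limit: exact McNemar reaches only 20% against 17%. The correction is worth making because it is almost free, but it concerns a secondary aim and does not threaten the primary one.

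**What to change.** In section 7.1, replace the single phrase with two rules.

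1. Any categorical pre/post change in the same participants is analysed with mid-p McNemar, reported with the paired difference in proportions and its confidence interval, or with a repeated-measures logistic model (GEE or mixed) across waves, with participant as the cluster.
2. Chi-square, or Fisher's exact test where cells are small, is kept for comparisons between different people at one wave, such as mutation groups or providers. Paired t-tests are kept for change in scores within the same people.

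It would also help to state whether the sun exposure and skin surveillance items are analysed as categories or as scores.

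The cost is a few lines of text and slightly more analysis work. No new data are needed. McNemar uses only participants with both waves, which any pre/post comparison already requires. The change does not cure low power in the mutation subgroups, so results there should rest on estimates and intervals.
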